## Abstract

**Background:**

There is growing demand for peer workers (people who use their own lived experience to support others in their recovery) to work alongside consumers to improve outcomes and recovery. Augmenting the workforce with peer workers has strong capacity to enhance mental health and recovery outcomes and make a positive contribution to the workforce within mental health systems and to the peer workers themselves. Technology-based applications are highly engaging and desirable methods of service delivery.

**Objective:**

This project is an exploratory proof-of-concept study, which aims to determine if a peer worker-led electronic mental (e-mental) health recovery program is a feasible, acceptable, and effective adjunct to usual treatment for people with moderate to severe mental illness.

**Methods:**

The study design comprises a recovery app intervention delivered by a peer worker to individual consumers at an adult mental health service. Evaluation measures will be conducted at post-intervention. To further inform the acceptability and feasibility of the model, consumers will be invited to participate in a focus group to discuss the program. The peer worker, peer supervisor, and key staff at the mental health service will also be individually interviewed to further evaluate the feasibility of the program within the health service and further inform its future development.

**Results:**

The program will be delivered over a period of approximately 4 months, commencing June 2017.

**Conclusions:**

If the peer worker-led recovery app is found to be feasible, acceptable, and effective, it could be used to improve recovery in mental health service consumers.

## Introduction

Peer work is a rapidly growing industry in Australia and internationally [1-4]. Current evidence suggests that peer work can make a positive difference in mental health services [1,5]; however, the role and definition of peer work is flexible and the practice is implemented in a variety of ways and settings [2]. Questions still remain as to how positive outcomes are best achieved and under what circumstances [5]. It is important to evaluate the feasibility of new peer work programs and to assess the acceptability of these programs for consumers, peer workers, and other staff.

Technology-based electronic mental (e-mental) health is a rapidly growing industry. These mental health interventions can be cost-effective to implement and there is growing evidence to support their effectiveness [6]. However, much more research is needed to understand how best to implement these tools in routine care [7]. Implementation challenges include low uptake and completion rates [8]. It has been proposed that peer support interventions may be able to increase the uptake and completion of e-mental health interventions [8]. The proposed project will assess the acceptability of presenting an e-mental health app led by a peer worker.

Peer support can be defined as “...a system of giving and receiving help founded on key principles of respect, shared responsibility, and mutual agreement of what is helpful” (page 1) [9]. Peer work can be paid or volunteer and workers use their lived experience of mental illness to inform their practice in providing emotional and social and instrumental support to other consumers [5,10]. Peer work is distinguished from other support work by several key factors, including (1) peer workers can instill hope through positive self-disclosure; (2) they can role-model skills for self-care and coping; and (3) they are able to develop a peer-to-peer relationship that is qualitatively different to a clinician-to-patient relationship [1]. The peer-to-peer relationship is characterized by trust, understanding, acceptance, and authentic empathy facilitated by shared or similar lived experiences [1,4,5].

Peers are found to be as effective or slightly more effective at producing desired outcomes, compared to usual staff, when employed in conventional roles in mental health services [1,11]. In these positions, peer workers have been found to increase the engagement of difficult to reach consumers, reduce rates of hospitalization and hospital stay duration, and decrease consumer substance use [1,5,12]. Peers can also be employed in diverse and flexibly defined peer specific roles [4]. There is evidence to suggest that in these circumstances peer workers can produce a range of benefits for consumers, particularly in regard to facilitating recovery. These benefits include an increased sense of independence and empowerment, improved self-esteem and confidence, improved social support and community integration, breaking down perceived stigma, and fostering a sense of hope through positive role modeling [1,5]. The current research protocol focuses on paid peer workers delivering a novel, technology-based recovery intervention in a public mental health care setting.

Peer work is not without challenges. The nature of peer support, particularly the requirement for self-disclosure, can make it difficult for peer workers to balance personal and professional boundaries in a workplace context [3-5,13]. In addition, the diverse and flexible definitions of peer work can lead to a lack of role clarity [13]. This can result in a range of workplace issues, including a lack of understanding and recognition of the value of peer work [3,4,13]. Effective training, appropriate management, professional supervision, and defined roles have been identified as key strategies for overcoming these challenges [3,13]. It is important to evaluate new peer work positions and programs to ensure the professional environment facilitates effective peer work and to identify areas that require improvement. In addition, reciprocity is a key element of peer support and peer workers have reported experiencing personal benefits from their occupation, including improved self-esteem and a sense of empowerment [4,5]. Through peer support training, voluntary work, and paid work, peers also have the opportunity to develop job skills and confidence [5,14,15]. Thus, peer work can provide people with a pathway to re-enter the workforce and facilitate a person’s continuing recovery. Due to the reciprocal nature of peer support, it is also important to determine whether peer-delivered services are acceptable for both consumers and peer workers.

### Aims

The aim of this project are to determine if a peer worker-led e-mental health recovery intervention is a feasible, acceptable, and effective adjunct to usual treatment for people with moderate to severe mental illness, as determined by the type of diagnosis, duration and/or intensity of symptoms and degree of functional impairment [16]. As an exploratory proof-of-concept study, the primary focus will be on elements of the program that consumers find useful or not useful, barriers and facilitators to implementation from the peer worker and service perspective, and primarily qualitative investigations of effectiveness for recovery outcomes. The findings of the research will help inform a larger investigation of the role of peer workers and e-mental health, which can guide the future implementation of these initiatives within existing mental health services.

### Objectives

The primary objectives of the study are (1) to investigate the feasibility and acceptability of embedding a peer worker in a public mental health service, from both the consumer and service perspectives; and (2) to assess the acceptability and effectiveness of a recovery-focused e-mental health program as an adjunct to treatment as usual for people with moderate to severe mental illness.

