### Project Design

The exploratory project design involves the post-intervention evaluation of a single cohort of participants using the recovery-focused e-mental health program. To inform this proof-of-concept study, we will also conduct interviews with the peer worker and mental health service staff and a focus group to collect qualitative perspectives with participants. The study protocol, in accordance with the Standard Protocol Items: Recommendations for Interventional Trials (SPIRIT) checklist [17], is shown in Multimedia Appendix 1.

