### Outcomes

#### Consumer Questionnaire

We will measure the participants’ perception of their own recovery using the Self-Identified Stages of Recovery (SISR) measure [24]. The SISR is a single-item scale describing stages of recovery and the participants’ perception of the stage of recovery with which they currently identify. Participants are asked to indicate which of 5 statements most closely describes how they have been feeling over the past month, with higher ratings indicating more positive perceptions of recovery. Examples of statements are:

I don’t think people can recover from mental illness. I feel that my life is out of my control, and there is nothing I can do to help myself.Question 1

I feel I am in control of my health and my life now. I am doing very well and the future looks brightQuestion 5

The single-item of the SISR has been argued to measure a unique aspect of recovery not assessed by continuous measures [25]. In addition, the single-item SISR has demonstrated reliability and concurrent validity [26] as well as convergent validity for the staged model of recovery [25].

Seven questions designed by consumer researchers will subsequently ask participants to rate their experience with the peer worker and the program on a 4-point scale from “Not at all” to “Yes definitely.” The questions were designed to explore the acceptability of a peer worker and an e-mental health program as a part of the service, as well as investigate recovery and self-efficacy. There is an open-ended section for any further remarks. The questionnaire will be conducted at the conclusion of the final session of the program delivery, within the usual time that consumers are attending the clinic for treatment.

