### Data Collection

All data collection will be conducted by members of the research team who will discuss protocols prior to commencing data collection to ensure consistency. Each participant will only be required to take part in the research on one occasion, with the exception of consumers who also choose to take part in the focus group. Due to the small sample and study location, no demographic data will be collected to minimize the chance of identifying individuals. All participants in the qualitative data collection will be advised that while every effort will be made to remove identifying information, they may still be identifiable from their comments.

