## Discussion

### Principal Findings

The current protocol describes an exploratory proof-of-concept study with results focused primarily on the feasibility of implementing the e-mental health program into service delivery models. We will also provide a post-intervention evaluation of the effectiveness of the program on recovery outcomes and the usefulness of the program from the consumers’ perspective. The study design is appropriate for the evaluation of an intervention and its feasibility in a real-world setting, using multiple perspectives and data collection methods. In addition, key strengths of the study include the consumer input into the evaluation design and the consideration of staff, peer worker, and consumer viewpoints in evaluating the intervention.

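### Effectiveness is a primary objective and a condition of the conclusion, but one end-of-program survey of a single uncontrolled cohort cannot establish it

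*Protocol article*

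**What the plan says.** **Claims.** In the protocol article, Objectives gives as the second primary objective "to assess the acceptability and effectiveness of a recovery-focused e-mental health program as an adjunct to treatment as usual". The abstract's Objective and the Aims section likewise set out to determine whether the program is effective. Principal Findings promises: "We will also provide a post-intervention evaluation of the effectiveness of the program on recovery outcomes". The abstract's Conclusions states: "If the peer worker-led recovery app is found to be feasible, acceptable, and effective, it could be used to improve recovery".

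**Design.** Project Design describes a "post-intervention evaluation of a single cohort of participants using the recovery-focused e-mental health program". Under Consumer Questionnaire, the SISR asks participants to indicate "which of 5 statements most closely describes how they have been feeling over the past month". The questionnaire is given at the end of the last session. It also holds seven study-designed questions on a 4-point scale, intended partly to explore recovery and self-efficacy. Data Collection adds: "Each participant will only be required to take part in the research on one occasion", the exception being those who also join a focus group. Analysis Strategy plans descriptive statistics, including the mean SISR score and the mean of each experience rating.

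**Scope.** The study is described as exploratory and proof-of-concept, and Aims says that effectiveness will be examined mainly through qualitative work. Limitations covers the difficulty of separating the peer worker from the app and the reliance on one peer worker. It mentions neither the missing baseline nor the missing comparator.

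**The concern.** An effectiveness statement about recovery says that people moved, and that the program moved them. The first part needs a starting value for the same people, or at least a reference value. The second needs some idea of what would have happened under usual treatment alone. The plan collects neither, yet effectiveness appears without qualification in a primary objective and in the abstract's conclusion.

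If the wording stands, a favourable end-of-program SISR mean may be reported as meeting the effectiveness half of the second objective, and the conclusion that the app could improve recovery would appear to follow. The results are meant to inform larger investigations and later guidelines, so an unsupported effectiveness claim could be carried forward.

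**Working it through.** **1. The plan's own figure.** Under Evaluation Survey the recruitment target is 30 consumers across 3 clinics, justified by staff expectations from clinic attendance. No alpha, power, effect size or SD is given, so there is no calculation to reproduce. The question is what the design can identify.

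**2. What effectiveness requires against what is observed.**

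- Change = mean at program end - mean before the program.
- Effect = change with the program - change under usual treatment alone.

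| Quantity | Observed? | Basis |
|---|---|---|
| Mean SISR at program end | Yes | Consumer Questionnaire; Analysis Strategy |
| Mean SISR before the program | No | Project Design; Data Collection |
| Change without the program | No | Project Design (single cohort) |
| Reference value or success threshold | No | None stated |

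**3. What the one observed quantity delivers.** The 95% CI half-width is t(0.975, 29) × SD / √30 = 2.045 × SD / 5.477 = 0.373 × SD. The documents give no SD for the SISR. Over an assumed range:

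- SD 0.8: 0.30 stages
- SD 1.0: 0.37 stages
- SD 1.2: 0.45 stages
- SD 1.4: 0.52 stages

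This is the precision of a level, not of a change.

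**4. The same end mean under different unseen baselines.** Take a hypothetical end mean of 3.8:

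- Baseline 3.2: 3.8 - 3.2 = +0.6 (improvement)
- Baseline 3.8: 3.8 - 3.8 = 0 (no change)
- Baseline 4.1: 3.8 - 4.1 = -0.3 (worsening)

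The planned data cannot distinguish these cases. A larger sample narrows the interval in step 3 but leaves step 4 as it is.

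**5. The other sources.** The seven experience questions are answered on the same single occasion. Focus groups (up to 10 consumers) and staff interviews take place at the end of the program. All can record whether people felt helped; none supplies a starting value or a comparator. Consumers are also invited to the survey only after completing the program, so a favourable result may partly reflect who stayed.

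**6. What a baseline or a comparator would add (illustration; n as assumed).** With the SISR also taken before the first session, 80% power at two-sided 5% (noncentral t) needs a standardised mean change of about 0.53 with 30 complete pairs, 0.60 with 24 and 0.66 with 20. That would show change, not its cause. Splitting 30 people 15 and 15 would detect only a standardised difference of (1.960 + 0.842) × √(2/15) = 1.02. These figures describe other designs and do not measure the defect.

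**The case against.** The best defence is that the study does not claim much. It calls itself exploratory, says its effectiveness work is mainly qualitative, plans only descriptive statistics, puts feasibility first in the Discussion, and words its conclusion conditionally. No test, change score or threshold is planned, so no quantitative improvement is formally asserted. This stands as a reason to lower the severity. It does not remove the mismatch: Objectives and the abstract's Conclusions carry no such qualifier, and the qualitative sources are post-program and uncontrolled as well. A separate analysis plan could not repair it either, because it cannot create a baseline that the design does not collect.

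Three stronger readings are tempting, and the documents do not support them.

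- *The SISR is the only recovery measure.* It is the only named scale, but the seven experience questions are also meant to explore recovery and self-efficacy.
- *The study gives no information at all on change.* The item wording is in Multimedia Appendix 3, which is not shown. Questions or focus-group prompts may ask about perceived change. That would be weak evidence, but not none.
- *The one-month recall period mistimes the SISR.* Session spacing is not stated, so how much of that month precedes the program is unknown. An end-of-program measure also need not cover time after the program.

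Nor do the documents say that the study must supply a variance of change for a later sample-size calculation, so its absence is no fault.

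**Conclusion.** The point holds: the effectiveness half of the second primary objective, and the word *effective* in the abstract's conclusion, cannot be supported by the planned data. The SISR mean at program end is equally compatible with improvement, no change and worsening. This follows from the design and rests on no assumed SD; the half-widths and detectable changes are illustrative only.

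A reader might infer that the study is unsound as a whole. The documents do not support that: the feasibility and acceptability objectives are untouched, the descriptive analysis suits them, and the exploratory scope is stated openly. This is a should-fix point about what the study says it can conclude, together with an unlisted limitation.

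**What to change.** **Needed.** Replace *effective* and *effectiveness* in the abstract's Objective and Conclusions, Aims, Objectives and Principal Findings. Suitable wording for the second objective would be: to assess the acceptability of the program and to describe consumers' self-rated recovery stage at its end and the benefit or usefulness they perceive. Add to Limitations that there is no baseline and no comparator, so neither change in recovery nor its cause can be established. No data collection or analysis changes; the cost is a less ambitious stated conclusion.

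**Optional.** Collect the one-item SISR before the first session and report how many consumers moved up, stayed or moved down in stage, with confidence intervals, labelled as uncontrolled. The form is short, but the change is not trivial:

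- Researchers currently approach consumers only after the program, and written consent precedes the questionnaire. Either research consent would have to come earlier, or a sealed, coded form would be released only for those who later consent.
- A linking code would be needed in a study that avoids demographic data to limit identifiability.
- An ethics amendment would be needed (two committees approved the study), and the Data Collection sentence on a single occasion would have to change.

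Even then the change could not be attributed to the program, so the rewording is needed either way.

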### Project Design

The exploratory project design involves the post-intervention evaluation of a single cohort of participants using the recovery-focused e-mental health program. To inform this proof-of-concept study, we will also conduct interviews with the peer worker and mental health service staff and a focus group to collect qualitative perspectives with participants. The study protocol, in accordance with the Standard Protocol Items: Recommendations for Interventional Trials (SPIRIT) checklist [17], is shown in Multimedia Appendix 1.

### Ethics Approval

The ethical aspects of this research were approved by the Australian Capital Territory (ACT) Health Human Research Ethics Committee (ETH.2.17.028) and The Australian National University Human Research Ethics Committee (ANU HREC 2017/338).

## Methods

### Researchers

Three of the researchers involved in the development and conduct of the study ([name]) have lived experiences of mental health problems and are currently working as consumer researchers. These experiences, together with a consumer and carer advisory group, offer unique insight into the development of the questionnaires and the evaluation of the study.

### Intervention

#### Peer Worker

A part-time (7 hours per week) peer worker with lived experience was recruited by ACT Health for the trial of a peer worker-led e-mental health program within its mental health service. The peer worker was required to have a qualification equivalent to a Certificate IV in Mental Health Peer Work, which is a professional course to develop specialist skills for working with clients facing mental health challenges [18]. The peer worker was required to (1) have direct personal lived experience of using mental health services; (2) have had a positive experience of recovery; and (3) have the ability and willingness to disclose personal experience of recovery in order to influence others positively. Their general duties were varied and included delivering programs, providing emotional support, developing trusting and professional relationships, and assisting other staff with the creation and review of recovery plans. The peer worker role statement is presented in Multimedia Appendix 2. The peer worker will be trained on the use and support of the Stay Strong app and will receive professional supervision and support for implementing the program by an experienced peer supervisor. However, they will not have experienced the recovery app as a client.

#### Stay Strong E-Mental Health App

The Stay Strong Care plan was developed and evaluated by [name] and developed into a mobile electronic app for iPads and other tablets in collaboration with Queensland University of Technology [19,20]. The app is a structured mental health and substance misuse intervention available through iTunes or Google Play. It is designed to be used as a collaborative tool between workers and service users and assists workers to guide service users through a structured, evidence-based mental health and substance use intervention.

Mental health workers may take on a range of roles when delivering e-mental health interventions, depending on the nature of the intervention and existing mental health skills of the worker [7]. Previous research with the Stay Strong app found that it may be most suitable for workers who are able to take on a coaching or therapist role [21]. In the current study, the peer worker will act in a coaching role and assist the person to complete the app and apply its concepts to their personal situation. We expect that the unique nature of the peer worker relationship, including the ability to provide hope for the future through role modeling, shared experience, and the capacity for assisting the person to disclose difficult personal issues [22] will facilitate and maximize the engagement of participants with the app content. Feedback from the peer worker will help inform the development of future protocols for the use of the app in mental health services.

Although the app was initially designed for use with Aboriginal and Torres Strait Islander service users and has some culturally-specific imagery and content [19], it has been approved by the authors for use in non-Aboriginal and Torres Strait Islander populations. It comprises a simple, highly visual design that does not rely on literacy and concentration levels. The Stay Strong tablet (iPad) app focuses on the consumer’s strengths and worries and helps them to set goals for change [23]. Consumers are first asked to identify the people in their life that help keep them strong, their relationships, and the role they play in the person’s life. They are then asked to identify their strengths in 4 areas of their life and this is represented visually as leaves on a tree. The more strengths they identify, the stronger and healthier the leaves become. Consumers also identify things in their life that take away their strength in the same 4 areas. The more worries that are input, the more the leaves on the tree wilt and turn yellow. This creates an interactive and visual representation of the parts in their life where they are strong and parts where they are not as strong. The app is designed for use by workers who have some training in mental health [19] but are not health professionals; its content focuses on goal setting and understanding strengths and vulnerabilities in relation to recovery.

